## Abstract

**Introduction:**

One in six stroke survivors continue to experience arm and language disability at 3 months post-stroke. This study aims to identify which model(s) of integrated UPper limb and Language Impairment and Functional Training (UPLIFT) show promise for people 3 months to 24 months post-stroke. We hypothesise that at least one promising UPLIFT model of rehabilitation will be identified.

**Methods and analysis:**

This is an adaptive Phase IIa master protocol umbrella design that includes four simultaneous Bayesian Optimal Phase II studies to evaluate individual UPLIFT interventions against prespecified objective performance criteria. The intervention is upper limb and language training at 2 or 4 hours/day, 5 days/week for 4 weeks, delivered either in person (severe stratum) or via telerehabilitation (mild–moderate stratum). Up to 160 adult participants will be recruited across six metropolitan/regional university or healthcare hubs spanning five Australian states. Baseline and post-intervention assessments are blinded. A promising response is defined as a composite binary outcome combining indicators of promise of efficacy, safety and feasibility. For each UPLIFT intervention, the proportion of participants with a promising response will be monitored at three equally spaced, predefined interim stopping points and one final analysis point (n=40 participants/study). An intervention will be stopped if too few promising responses are observed.

**Ethics and dissemination:**

Ethical approval was obtained from The Royal Melbourne Human Research Ethics Committee. All participating sites obtained local governance approval. All recruited participants will provide informed consent. Trial results will be disseminated through peer-reviewed publications and presented at major stroke and rehabilitation conferences.

**Trial registration number:**

ACTRN12622000373774.

WHAT IS ALREADY KNOWN ON THIS TOPICHigh-dose upper limb or language rehabilitation can promote recovery after stroke—even in the late subacute (>3 months) and chronic (>6 months) phases of recovery.WHAT THIS STUDY ADDSThis trial will identify if any integrated UPLIFT (UPper limb and Language Impairment and Functional Training) intervention dose(s) have sufficient promise to take forward to a seamless Phase IIb–III trial.HOW THIS STUDY MIGHT AFFECT RESEARCH, PRACTICE OR POLICYThis trial implements a novel early phase master protocol adaptive umbrella trial process to screen potential interventions and advance the generation of evidence in stroke recovery to avoid progression of futile treatments to late phase testing. This process is translatable to test pharmacological and non-pharmacological interventions for neurological conditions.

## Introduction

 One in six (~15%) survivors need assistance to complete arm (eg, grasping) and language (eg, conversing) functions 3 months post-stroke.^1^ Enabling long-term arm and language recovery are priorities for better living after stroke.^2^ Failure to address these limitations during community living results in unmet needs.^2^ The potential for recovery of arm and language functions can persist into the late-subacute (>3 months) and chronic (>6 months) phases of recovery post-stroke^3^,^5^ often via community rehabilitation programmes.^6^ The magnitude of gain across both upper limb^5 7 8^ and language^4^ functions appears to reduce as time post-stroke increases. Greatest gains have been observed over weeks to months rather than years post-stroke. It is critically important to reduce potential heterogeneity introduced by post-stroke disability chronicity in the context of a clinical trial. Focusing on the first 24 months post-stroke and defining subpopulations may allow the field to attempt to challenge the recovery window boundary while minimising potential heterogeneity when testing new intervention approaches.

Treatment targeting one functional limitation may improve another. Preliminary evidence has demonstrated that upper limb intervention leads to improvements in both upper limb and language outcomes^9 10^; motor cortex stimulation can effect language (aphasia) outcomes^11^; and that sequential upper limb and language sessions may enhance recovery of both.^12^ An integrated intervention approach that directly harnesses interrelated arm and language neural processes could be key to unlocking better recovery post-stroke. Integrated function reflects our real-world. For example, writing places demands on the motor (hold the pen) and language (produce the words) systems. Despite this, current care largely treats each functional limitation in isolation.

This trial of integrated intervention seeks to enhance recovery by considering dose, subpopulation and mode of integrated intervention. The current dose of upper limb or language therapy in the Australian outpatient, community living population is poorly reported. Pragmatically, it can range from no therapy through to daily therapy depending on post-stroke needs, availability of services and access to services. In clinical trials, the largest upper limb improvements in activity have been demonstrated for interventions providing greater than 2 hours/day over 4–5 days/week.^13^ The largest language improvements have been linked to 2–4 hours of intervention given over 4–5 days/week.^4^ Therefore, a minimum of 2 hours is an essential starting dose for trials aiming to improve either upper limb or language recovery.^13^ Stroke is heterogeneous and subpopulations are an important consideration. The ability to activate a muscle (eg, flicker of movement) as compared with picking up a cup indicates a different level of functional ability, as does the ability to say a single word compared with a simple sentence. Integration of subpopulation stratum based on function can help to move the field from one-size-fits-all towards tailored and targeted treatment programmes. Finally, the mode of delivery (eg, in-person, telerehabilitation) can be modified based on functional level. In the context of severe functional limitations (eg, flicker of movement or single word utterance), it may be more challenging to deliver complex and high dose interventions via telerehabilitation and in-person may be warranted. Enriching our understanding of who benefits from what intervention mode could enhance how post-stroke rehabilitation resources are used and how people can access services (eg, rural and remote areas).

With limited understanding of the optimal dose and safety profile of an integrated intervention, immediately initiating a late phase trial may expose many patients to a subtherapeutic treatment or potentially lead to harm.^1^ A Phase IIa trial is therefore most appropriate to generate data on dose, safety and feasibility. Recent trial design innovations, including a single overarching trial structure (ie, master protocol) within an umbrella design,^14^ provide an opportunity to test a given intervention (dose, mode) within a subpopulation (severity) to identify the most promising intervention(s) to take forward to a later phase trial. Each treatment:subpopulation (ie, study) can be driven by participant response at predefined interim stopping points^14^ that should exceed a prespecified objective performance criterion, that is, a value that is based on previously available relevant data or meta-analysis.^15^ Therefore, in such a design, comparison is not between groups but rather to the specified value, so that none, some or all interventions tested can demonstrate sufficient promise to progress to the next phase of testing. A good participant response can integrate dose, safety and signal of efficacy consistent with the purpose of a Phase IIa trial. If too few promising participant responses are observed, the intervention can be stopped, and future participants directed into more promising interventions. This can directly benefit current trial participants and attempt to fast-track the discovery process compared with conducting multiple separate trials.^14^

We will undertake a Phase IIa umbrella trial of integrated UPper limb and Language Impairment and Functional Training (UPLIFT) during community living after stroke. The aim of this umbrella, multicentre clinical trial is to identify the most promising integrated UPLIFT model for people 3 months to 24 months post-stroke. An umbrella design provides a single overarching master protocol structure to simultaneously evaluate individual UPLIFT interventions (studies) to identify the most promising approach. We hypothesise that at least one promising UPLIFT model of rehabilitation will be identified that can be taken forward to a Phase IIb–III trial.

## Methods and analysis

### Design

This is a multicentre, assessor-blinded, adaptive umbrella Bayesian Optimal Phase IIa (BOP2) trial reported per SPIRIT (Standard Protocol Items: Recommendations for Interventional Trials)^16^ and adaptive trial extension guidelines.^17^ This trial includes four simultaneous studies to evaluate individual UPLIFT interventions against prespecified objective performance criteria.^15^
Figure 1 outlines trial design, decision logic and intervention for the four studies.

**Figure 1 F1:**
[figure not shown]
UPLIFT (UPper limb and Language Impairment and Functional Training) trial overview. (**A**) Umbrella design, strata and randomisation groups. (**B**) BOP2 decision logic for each individual stratum. (**C**) Primary outcome definition. (**D**) Intervention overview including assessment and fidelity monitoring.

### Participant population

Up to 160 people with stroke will be recruited across six metropolitan and regional hubs across five Australian states. Eligibility criteria are defined in box 1.

Box 1Eligibility criteriaInclusionAdults aged 18 years or above.Clinical diagnosis of hemispheric stroke (ischaemic/haemorrhagic) between 3 months and 24 months prior to recruitment.If repeat stroke, no residual arm or language deficit from prior stroke(s).Presence of stroke-related upper limb impairment (minimum flicker of movement) and language (aphasia) impairment (minimum single interpretable word output).Able to follow single-stage commands.Able to provide informed consent, or make medical decisions, if required.Appropriate candidate for home therapy if required, and willingness to use required technology.ExclusionBaseline score(s) that prevent required change on at least one priority outcome.No residual upper limb or language stroke-related deficit.Severe comorbid medical illness, eg, active intervention for cancer; concomitant neurological condition, eg, Parkinson’s disease; psychiatric illness, eg, uncontrolled bipolar disorder; other diagnosis deemed by the investigator to make a participant unlikely to be able to fully participate in all study procedures, eg, pain on movement.Life expectancy <3 months.

### Participant identification and consent

Potential participants can self-refer via the Stroke Foundation of Australia EnableMe consumer platform (https://enableme.org.au/community/research) or a clinician could refer with stroke survivor consent. A brief aphasia-friendly study flyer is available in written and aphasia-friendly video (https://www.youtube.com/watch?v=piuyMFZsepg) formats. All referrals are reviewed by the University of Melbourne UPLIFT Trial Central Team who conduct an email or phone prescreen followed by a video consultation to confirm eligibility (ie, upper limb and language function visual examination, check telehealth capacity if required). All potential participants are provided information in written (standard and aphasia-friendly) and video (standard https://youtu.be/9sLgo4nIakY and aphasia-friendly https://youtu.be/L9OaWALB2t0) formats. Ethical approval was granted to assess priority outcomes (defined below) during screening to ensure that the required change could be achieved per eligibility criteria. All participants or their representative provide written informed consent. Representative consent is not available at New South Wales or Western Australian sites.

### Primary outcome

A single binary composite primary outcome (achieved good outcome: yes or no) will be applied to define a good outcome. A good outcome is comprised of four binary items that are achieved at an individual participant level:

Improvement at or beyond the predefined outcome-specific threshold on at least ONE priority outcome, ANDNo deterioration on ANY priority outcome beyond the predefined threshold, ANDGreater than or equal to 75% time-on-task of the allocated dose target across the intervention administration phase, ANDNo serious adverse event related to the intervention.

The UPLIFT trial executive identified four priority outcomes based on psychometric properties and international consensus statement recommendations including the Stroke Recovery and Rehabilitation Roundtables^18^ and Research Outcome Measurement in Aphasia.^19^ Published literature informed group discussion and final selection of a corresponding predefined priority outcome-specific threshold:

Fugl Meyer Upper Limb (impairment): change greater than or equal to 5.25 points.^20^Box and Block Test (activity): change greater than or equal to 5.5 blocks.^21^Western Aphasia Battery-Revised Aphasia Quotient (impairment): change greater than or equal to 5 points.^22^Communicative Effectiveness Index (CETI, activity): change greater than or equal to 10.37 points.^23^

All priority measures are performed by the participant except for the CETI. The CETI is completed by a caregiver, family member or partner of a person with aphasia to assess their functional communication abilities in everyday situations. Post-intervention CETI scoring is independent of baseline score knowledge. If a participant does not have an appropriate person to complete the CETI, the remaining three priority outcomes will only be used to inform good outcome achievement.

### Secondary outcomes

Secondary outcomes are collected at baseline and post-intervention (table 1). A formal process evaluation is not required in this early phase trial. We included a simple evaluation to probe intervention dose, content and access barriers and enablers. All assessors are trained (review of written and audiovisual materials, virtual training session, competency scoring where available) in primary and secondary outcomes before completing any trial-related assessments.

**Table 1 T1:** UPLIFT trial schedule of enrolment, intervention and assessments

	Study period				
	Enrolment	Baseline		Intervention	Post-intervention
TIME POINT	<Week 0	Week 0		Week 1–4	>Week 4
ENROLMENT:					
Eligibility screen	X				
Informed consent	X				
Allocation			X		
INTERVENTION:					
Mild–moderate telerehabilitation, 2 hours/day				X	
Mild–moderate telerehabilitation, 4 hours/day				X	
Severe in-person, 2 hours/day				X	
Severe in-person, 4 hours/day†*				X	
Multidimensional dose recording*				X	
Fidelity video recording				X	
Upper limb weekly assessment: Rating of Everyday Arm and hand use in the Community and Home				X	
Language weekly assessment: Visual Analogue Scale for communication				X	
ASSESSMENT†:					
Demographic Information		X			
Stroke Information		X			
modified Rankin Scale		X			X
Fugl Meyer Upper Limb Assessment*		X			X
Box and Block Test*		X			X
Western Aphasia Battery-Revised*		X			X
Communicative Effectiveness Index scale*		X			X
9-Hole Peg Test		X			X
Action Research Arm Test		X			X
Rating of Everyday Arm and hand use in the Community and Home		X			X
Discourse (video-recorded)		X			X
Reaching for a cup (video-recorded)		X			X
Trail Making Test B		X			X
Clock Drawing Task		X			X
Boston Naming Test		X			X
Stroke and Aphasia Quality of Life Scale-39		X			X
National Institute of Health Stroke Scale		X			
Process evaluation		X			X
Adverse events*		X		X	X

* Contributes to single binary composite primary outcome.

† Baseline assessments by blinded assessor completed 5 days (±2 days) prior to Intervention onset. Post assessments by blinded assessor completed within 5 days (±2 days) of Week 4 Day 5.

### Safety outcomes

All adverse events will be recorded from the time of consent until the post assessment has been completed (end of study). Adverse event documentation will include start and stop dates, action taken, outcome, intensity and relationship to study intervention (causality). Adverse events will be classified as serious or not and intervention related or not. In addition, all serious adverse events will include a rating of severity, causality and expectedness. All safety events (serious adverse events and adverse events) will be reviewed and a final classification documented by the medical monitor.

### Randomisation and blinding

Randomisation to 2 or 4 hours of intervention dose is within strata (severe, mild–moderate) to achieve better representativeness of individual studies as well as better sequential balance within individual studies given the frequent nature of interim analyses in this early phase design. Randomisation is not used to enable statistical inference of comparative effect as the nature of this design does not assume comparison of various intervention doses. Randomisation is via a centralised allocation system designed by the trial statistician (LC). Participants allocated to the severe strata must meet the minimum entry criteria (box 1). Participants allocated to the mild–moderate strata must: (1) have baseline scores that permit the required threshold change on all priority outcomes, (2) be able to pick up an empty standardised cup and raise it off the table for 5 s without drift of the cup, hand, wrist or elbow to the table and (3) be able to say a correct, basic sentence, for example, ‘I drink water’. Upper limb and language tasks for strata severity rating are video-recorded and evaluated by two study personnel. Initial raters discuss the outcome if there is a discrepancy before a third person reviews the video recording. Each BOP2 study can have up to four cohorts (n=10) and no cohort can have more than 50% of participants who are more than 12 months post-stroke. On completion of strata severity rating, participants are randomly allocated within each stratum to 2 or 4 hours/day. Forced randomisation is possible in the event a clinical site faced a situation when an eligible trial participant was to be randomised to a treatment not available to be delivered per protocol at the site.^24^

### Sample size calculation

While Bayesian in nature, our design ensures appropriate frequentist characteristics (power=0.8, alpha=0.05). The sample size was estimated using an online BOP2 design tool.^25^ Allowing for three equally spaced interim stopping points (n=10, n=20, n=30) and a final decision point analysis (n=40), a sample size of 40 participants per study was estimated using the null hypothesis rate of upper limb and language recovery of 0.5 vs alternative hypothesis rate of recovery of 0.7.^26^

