### Statistical analysis

A statistical analysis plan will be completed prior to database lock. A participant will be deemed to have not achieved a good outcome if withdrawal is for trial-related reasons (eg, intervention load). A participant will be replaced if withdrawal is for non-trial related reasons (eg, COVID-19). An independent (LO) member will prepare all data summaries for interim and final analyses. Two people will review interim data ([name] content expert and LC statistical expert), protocol deviations and file notes against a priori defined rules to rate each binary item of the composite primary outcome as achieved or not. For efficacy, the change between baseline and post-intervention is calculated for each priority outcome to determine if there is improvement or decline at or beyond the predefined outcome-specific threshold. The first binary item is considered achieved by a participant if at least one priority outcome improves beyond the predefined threshold. The second binary item is considered achieved if the participant does not decline beyond the threshold for any priority outcome. For feasibility, the proportion of time-on-task is averaged across the intervention administration period (Weeks 1/2/3). The third binary item is considered achieved by a participant if their average time-on-task is ≥75%. For safety, all serious adverse event outcomes are reviewed for intervention relatedness. The fourth binary item is considered achieved by the participant if they have no intervention-related serious adverse event. If all four binary items are rated achieved, then a participant is deemed to have made a good outcome. Recruitment to a given study will continue (up to a maximum of n=40) if sufficient participants achieve a good outcome on the single binary composite primary outcome at interim (see figure 1). A study will be stopped if insufficient participants achieve a good outcome at interim. Online supplemental A provides an interim analysis template. All secondary outcomes will be reported at baseline, post-intervention and baseline-post-intervention change (median, SD).

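### The 0.5 versus 0.7 criterion is worded as a rate of recovery, but the decisions count a four-item composite, so as worded the 80% power does not apply to the monitored endpoint

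*Protocol article*

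**What the plan says.** In the protocol article, the Sample size calculation section gives the two design rates as a "null hypothesis rate of upper limb and language recovery of 0.5 vs alternative hypothesis rate of recovery of 0.7", with a citation to an outside source. It states that "our design ensures appropriate frequentist characteristics (power=0.8, alpha=0.05" and sets "three equally spaced interim stopping points (n=10, n=20, n=30) and a final decision point analysis (n=40". It does not mention the composite.

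The Primary outcome section defines the endpoint: "A good outcome is comprised of four binary items that are achieved at an individual participant level". The items are:

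1. improvement past threshold on at least one of four upper limb or language measures;
2. no decline past threshold on any of them;
3. at least 75% time-on-task;
4. no intervention-related serious adverse event.

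The Statistical analysis section confirms the AND rule: "If all four binary items are rated achieved, then a participant is deemed to have made a good outcome". It applies the continue-or-stop decision to that composite, and it scores a withdrawal for a trial-related reason as not achieving a good outcome.

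The Introduction explains that "comparison is not between groups but rather to the specified value", and describes the criterion as "a value that is based on previously available relevant data or meta-analysis".

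**The concern.** With no control comparison, 0.5 is the only benchmark in each study and 0.7 is the only target. Time-on-task and freedom from related serious adverse events are not recovery. A recovery rate taken from earlier data therefore needs converting before it can serve as the null or alternative for the composite. The article shows no conversion and does not say that one was made.

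If 0.7 is a recovery rate, an intervention that reaches it will have a lower composite rate whenever some improvers miss another item. Its chance of being declared promising is then below the stated 80%. Each study feeds a go or no-go decision for a Phase IIb–III trial, so a reader needs to know which quantity the criterion describes.

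**Working it through.** **Inputs from the article.** Rates 0.5 and 0.7; looks at 10, 20, 30 and 40 participants; power 0.8; alpha 0.05, read as a one-sided ceiling because each study is compared with a fixed value.

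**Assumed, because the decision figure is not shown.** A BOP2 rule with a Beta(0.5, 0.5) prior that stops when Pr(p > 0.5 | data) < λ(n/40)^γ. λ and γ are chosen to maximise power subject to type I error of at most 0.05.

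**Step 1: reproduce the stated design.** The best boundary found stops at ≤3/10, ≤9/20 and ≤16/30, and declares promise at ≥26/40. The probability of being declared promising comes from exact binomial convolution: add a Binomial(10, p) block at each look and remove the stopped outcomes.

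- p = 0.50: 0.0397
- p = 0.70: 0.803

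As a check, the final rule alone (≥26/40, no interim looks) gives 0.0403 and 0.807. The stated alpha ceiling and power are therefore reproduced, provided that 0.5 and 0.7 are rates of the outcome actually counted.

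**Step 2: relate the improvement rate to the composite rate.** Let r be the item 1 rate and q the share of improvers who also meet items 2 to 4. Then

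composite rate = r × q ≤ r.

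The direction needs no assumption. The size does, because the article gives no value for q. The table takes r = 0.5 under the null and r = 0.7 under the alternative, with the boundary unchanged.

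| Assumed q | Null composite | P(promising) | Alternative composite | P(promising) |
|---|---|---|---|---|
| 1.00 | 0.500 | 0.040 | 0.700 | 0.803 |
| 0.95 | 0.5 × 0.95 = 0.475 | 0.019 | 0.7 × 0.95 = 0.665 | 0.645 |
| 0.90 | 0.5 × 0.90 = 0.450 | 0.009 | 0.7 × 0.90 = 0.630 | 0.462 |
| 0.85 | 0.5 × 0.85 = 0.425 | 0.003 | 0.7 × 0.85 = 0.595 | 0.291 |
| 0.80 | 0.5 × 0.80 = 0.400 | 0.001 | 0.7 × 0.80 = 0.560 | 0.160 |

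Power falls steeply with q. The type I error falls too, so on this reading the rule is conservative under the null.

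**The case against.** The strongest reply is that recovery is one loosely used word. The Abstract defines a promising response as efficacy, safety and feasibility combined, and monitors that proportion against the performance criteria. The Introduction says that participant response should exceed the criterion and that a good response can integrate dose, safety and signal of efficacy. On that reading 0.5 and 0.7 are already composite rates. The arithmetic cannot decide between the readings, because N = 40 reproduces for any binary endpoint with those rates. This stands, and it makes the power loss conditional.

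It also stands that the q values are assumptions, and that equating recovery with item 1 is an interpretation. Item 1 needs improvement in only one domain, whereas the sizing text names both, and the cited source is not available here. Stopping a model for poor feasibility or safety is intended by the design and is no error.

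Three stronger readings are tempting, and the article does not support them.

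- A reader might infer that neither stated error rate applies. Both hold if the rates are composite rates. If they are not, the type I error stays under 0.05 in the direction worked above.
- A reader might infer that an inert model can pass because item 1 offers four chances. If each measure crosses its threshold without benefit with an assumed, independent probability of 0.10 or 0.16, any-of-four is 1 − 0.90⁴ = 0.34 or 1 − 0.84⁴ = 0.50. Any-of-three, for participants without a CETI respondent, is 0.27 or 0.41. None of these materially exceeds the 0.5 null, and items 2 to 4 lower them further. Exceeding it clearly takes a higher assumed input: 0.20 per measure gives 0.59.
- A reader might infer an error from using one criterion in both strata, since only mild–moderate participants must "have baseline scores that permit the required threshold change on all priority outcomes". A common benchmark is a design choice, and the article says how a missing CETI is handled.

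The reply does not remove the central point. The article leaves some detail to the full protocol, but here it names a quantity, and that quantity is not the one monitored.

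**Conclusion.** The concern holds in conditional form. As worded, the design rates describe recovery while the decisions count the four-item good outcome, and nothing links the two. If 0.7 is the improvement rate, power for the monitored endpoint is below 0.80: about 0.64 if 95% of improvers meet the other items and 0.46 if 90% do, with a conservative type I error. If 0.5 and 0.7 were meant as composite rates, the operating characteristics stand (about 0.04 and 0.80) and the fault is one of wording and justification. These figures rest on a reconstructed boundary and assumed values of q. The point calls for a clear correction but does not invalidate the design.

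**What to change.** In the Sample size calculation section, state 0.5 and 0.7 explicitly as rates of the four-item good outcome and justify them on that scale. If 0.7 was a recovery rate, say so and restate the power for the composite.

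Keep n = 40 and the boundaries. Add a short table of the probability of being declared promising over composite rates of about 0.40 to 0.70. With the reconstructed boundary it would read:

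| Composite rate | 0.40 | 0.45 | 0.50 | 0.55 | 0.60 | 0.65 | 0.70 |
|---|---|---|---|---|---|---|---|
| P(promising) | 0.001 | 0.009 | 0.040 | 0.131 | 0.314 | 0.567 | 0.803 |

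The trial's actual boundary should replace the reconstruction. Report the four items beside the composite, so that a stop can be attributed to efficacy, feasibility or safety; the items are already rated separately.

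The cost is wording and two short tables, with no extra participants. The downside is that the stated power may become less favourable.
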